### Objectives {7}

The primary objective is to evaluate the impact of an analytical and repetitive ankle mobilisation programme (combined with conventional rehabilitation including repetitive gait training) on comfortable walking speed over 10 m at the end of the intervention.

The secondary objectives are (1) to evaluate the impact of the programme on social participation at 6 months and 1 year, and to measure its evolution, (2) to evaluate the impact of the programme on the spatiotemporal parameters of walking at the end of the intervention and to measure their evolution at 6 months and 1 year, (3) to evaluate the impact of the programme on the progression of walking speed at 6 months and 1 year, (4) to evaluate the impact of the programme on dorsiflexor muscle strength and to measure its progression over time, at baseline and just after the intervention, along with at 6 months and 1 year of follow-up, (5) to evaluate the impact of the programme on the use of technical aids and on the number of falls between 6 months and 1 year, and (6) to evaluate the relationship between dorsiflexor muscle strength, walking speed and social participation.

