### Outcomes {12}

All testing sessions will be conducted by one physical therapist and one research assistant (per centre). Both evaluators will be blinded to the treatment.

Clinical and physical outcome measurements will be administered to the patients at baseline, immediately after 6 weeks of treatment, 6 months and 1 year after treatment (Fig. 1).

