**Fig. 1 Fig1:**
[figure not shown]
Schedule of enrolment, intervention, assessment and follow-up

The *primary outcome* is defined as walking speed measured over 10 m at the end of the intervention (6 weeks).

The *secondary outcome* includes social participation evaluated at 6 months and 1 year, walking spatiotemporal parameters measured at each visit, walking speed measured at 6 months and 1 year, along with dorsiflexor strength evaluated at each visit.

The use of technical aids to walk and the number of falls will be described.

Finally, correlations between walking speed/dorsiflexor muscle strength and walking speed/social participation will be studied.

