#### The following secondary endpoint analyses:

The comparison of the mean difference of the SIPSO score between 6 months and 1 year (T_12M_ – T_6M_) will be performed by means of a Student's t test if the variable follows a normal distribution (Shapiro-Wilks test) or by a non-parametric Mann-Whitney test otherwise.The comparison of the progression of the 4 spatiotemporal parameters selected (duration of the stance and swing phases, step cadence and variability) will be performed using a mixed generalised linear regression.The comparison of the progression of the 2 parameters describing the force of the dorsi-flexor muscles (peak torque in Nm and active amplitude in degrees) will be performed using a generalised linear regression.The comparison of the proportion of patients who used a technical aid will be performed by a Pearson’s chi [2] test or a Fisher’s exact test if at least one theoretical number is <5). The comparison of the number of falls per patient after 6 months will be performed by a binomial negative regression.Correlations between [1] dorsi-flexor muscle strength (2 parameters) and walking speed at 6 weeks, 6 months, and 1 year [2]; dorsi-flexor muscle strength (2 parameters) and SIPSO score at 6 months and 1 year [3]; walking speed and SIPSO score at 6 months and 1 year will be performed using the Pearson or Spearman correlation coefficient test depending on the conditions of application.

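### Progression of dorsiflexor strength over four visits is assigned a regression with no within-patient term, while gait parameters from the same visits get a mixed model

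*Protocol article*

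**What the plan says.** Outcomes {12} schedules the assessments "at baseline, immediately after 6 weeks of treatment, 6 months and 1 year after treatment", which makes four per patient. The text after Fig. 1 lists "walking spatiotemporal parameters measured at each visit" and, in the same sentence, "along with dorsiflexor strength evaluated at each visit". The fourth secondary objective in Objectives {7} is to assess the programme's effect on strength and "to measure its progression over time, at baseline and just after the intervention, along with at 6 months and 1 year of follow-up".

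The secondary endpoint analyses under Statistical methods {20a} then take two outcomes with this shared visit schedule in consecutive sentences:

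- Gait: the comparison of progression for the four parameters "will be performed using a mixed generalised linear regression".
- Strength: the comparison of progression for the two parameters, "peak torque in Nm and active amplitude in degrees) will be performed using a generalised linear regression".

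The document names no random effect, estimating-equation method, robust variance, repeated-measures covariance or change score for strength.

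**The concern.** Asking how strength progresses over four visits is a repeated-measures question. Values from one patient are correlated, and a generalised linear regression without a within-patient term takes its rows to be independent. The preceding sentence shows that the authors write the mixed form when they want it. The strength model has therefore been stated, in a form that differs from its neighbour for no given reason. It is not simply a detail left to an analysis plan.

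What is at stake is the strength result itself. The Introduction ties dorsiflexor strength to walking, and the Discussion expects less loss of strength in the experimental group. With 60 patients planned, a test that discards the within-patient information could easily miss a real difference in progression.

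**Working it through.** **The plan's own figure.** None is given for the strength analysis. The only sample-size calculation, in Sample size {14}, is for walking speed and is not in dispute. The pooled variance is (0.09² + 0.11²)/2 = 0.0101, so n per group = 2 × (1.960 + 1.282)² × 0.0101 / 0.09² ≈ 26.2, rounded up to 27. That agrees with the stated 54 in total.

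**Inputs.**
- From the document: four visits per patient; two groups, 1:1; 27 per group evaluable.
- Two-sided 5% level: stated for the primary outcome and applied here to strength.
- Assumed: equal variance at each visit and the same correlation ρ between any two visits of one patient. The document gives no ρ, so 0.5, 0.7 and 0.8 are shown, with 0.3 and 0.9 as outer cases.
- Assumed: 90% power for the strength contrast under a correct model, as a reference point only. The protocol sets 90% for walking speed and states no power for strength.

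**Progression (group by visit), the planned comparison.** For the between-group difference in change from one visit to another, with n per group and variance σ²:
- variance the independence model reports: 4σ²/n
- true variance: 4σ²(1 − ρ)/n

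The reported standard error is therefore too large by a factor of 1/√(1 − ρ). With 90% power under a correct model, the standardised effect is 1.960 + 1.282 = 3.242. The power left is P(Z > 1.960/√(1 − ρ) − 3.242), and the true type I error is 2 × [1 − Φ(1.960/√(1 − ρ))].

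| ρ (assumed) | Reported SE too large by | Critical value less effect | Power left, from 90% | True type I error |
|---|---|---|---|---|
| 0.5 | 1.41 | 2.772 − 3.242 = −0.470 | 68% | 0.6% |
| 0.7 | 1.83 | 3.578 − 3.242 = 0.336 | 37% | 0.03% |
| 0.8 | 2.24 | 4.383 − 3.242 = 1.141 | 13% | below 0.01% |

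At ρ = 0.3 the factor is 1.20 and the power left is 82%. At ρ = 0.9 they are 3.16 and 0.2%.

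**Group effect averaged over the four visits, which the plan does not state.** Here the true variance is 1 + 3ρ times the reported one, so the reported standard error is too small. The type I error is 2 × [1 − Φ(1.960/√(1 + 3ρ))].

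| ρ (assumed) | √(1 + 3ρ) | True type I error |
|---|---|---|
| 0.5 | 1.58 | 22% |
| 0.7 | 1.76 | 27% |
| 0.8 | 1.84 | 29% |

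**Simulation check.** Ordinary regression was fitted to all rows, with 27 per group, four visits, no true effect and 4,000 runs. The three-degree-of-freedom group-by-visit test rejected in 0.15%, 0% and 0% of runs at ρ = 0.5, 0.7 and 0.8. The averaged group effect was rejected in 21%, 26% and 30%. With ρ = 0, both tests held about 5%. The direction and size of both errors agree with the formulas.

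**The case against.** The strongest reply is that the document never says that visits are treated as independent. That is inferred from the absence of one word, which may be a slip. The sentence fixes neither the data layout nor the covariance. An estimating-equation fit, or a change score with one row per patient, would be valid and could loosely carry the same name. The same section does use a one-value-per-patient change for the SIPSO score. A condensed article may also leave covariance details to an analysis plan.

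Part of this stands. The error is conditional on fitting the model as worded to all visits, and intent cannot be settled from the text. It does not remove the inconsistency. The SIPSO change score is spelled out, so one cannot simply be read into the strength sentence, and the neighbouring sentence names the mixed form for outcomes with the same schedule.

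A reader might also infer that the strength analysis will produce false positives in more than 20% of tests. The documents do not support that. The inflation belongs to a group effect averaged over all four visits, including the pre-treatment one, and the plan states a comparison of progression. For that comparison the error runs the other way.

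Two further limits hold. The correlations, their equality across visits and the 90% starting point are all assumptions. And Outcome measurements names only peak torque as the strength data collected, so measurement of active amplitude at all four visits is less explicit.

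**Conclusion.** The point holds in a conditional form, as a should-fix for a secondary endpoint. The strength model is inconsistent with the gait model for the same visits. Followed literally on all visits, it gives a wrong standard error for any within-patient correlation above zero.

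For the planned progression comparison, the consequence is a conservative test and lost power, to the extent tabulated above. Those figures rest on assumed exchangeable correlations and a borrowed 90% reference power. They show the order of the loss and do not predict it for this trial. Inflated type I error, about 22% to 29% over the same correlations, would arise only if an averaged group effect were tested.

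The text does not justify saying that the strength standard errors will certainly be wrong, because a valid repeated-measures analysis may have been intended. The primary comparison of walking speed at 6 weeks and the sample size are untouched.

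**What to change.** Replace the strength model with the mixed model named for the gait parameters, or an equivalent repeated-measures model. It should have group, visit and group-by-visit terms and a within-patient random effect or covariance. If baseline strength enters as a covariate, keep only the three post-baseline visits as outcome rows, so that baseline is not both outcome and predictor. Baseline and centre adjustment are optional here: the article does not give them for the gait model, and this correction does not depend on them.

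If a change score or estimating equations were intended, saying so would also resolve the point. The cost is one line of protocol or analysis-plan wording, with no new data, visits or patients.

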### Eligibility criteria {10}

The study is presented to all patients hospitalised in the physical medicine and rehabilitation departments for a first stroke and meeting all other eligibility criteria: (1) they are within 15 days to 3 months of stroke onset (ischaemic or haemorrhagic); (2) they have persistent foot lift deficiency (Medical Research Council testing: MRC<5); (3) they are able to walk alone at least 10 m with or without technical assistance; (4) they do not have pain in the paretic lower limb (AVS<2); and (5) they are cleared to participate in physical therapy.

Patients will be excluded from the study if they (1) have cognitive or phasic disorders preventing them from understanding the instructions: Boston Scale BDAE<2; (2) had gait disorder before the stroke; (3) have fixed contracture of the ankle (irreducible equinus); (4) are too spastic: Modified Ashworth (MAS) greater than or equal to 4; (5) are pregnant, have a desire for pregnancy or are breastfeeding; and (6) are under curatorship or guardianship or under the protection of justice.

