### Participant timeline {13}

#### Inclusion

The inclusion visit will be conducted by the physician within 1 week of the pre-inclusion visit. It is carried out during hospitalisation, between 15 days and 3 months post-stroke. The investigator will perform a clinical examination to verify the inclusion and non-inclusion criteria. Once the criteria have been verified, the patient and investigator will sign the informed consent form.

The investigator will collect data on the patient's stroke pathology.

The clinical examination will then be completed to provide clinical scores: severity of the stroke (National Institute of Health Stroke Score; NIHSS), passive and active range of motion of the ankle (P-ROM, A-ROM: manual measurement), motor control of the injured lower limb (De Meurisse Motor Index; MI), assessment of spasticity of the posterior leg compartment (Modified Ashworth Scale; MAS), level of functional independence (Barthel index; BI) and walking autonomy (Functional Ambulation Classification; FAC) with collection of the technical aids used and the number of falls.

This clinical evaluation will be completed by instrumental evaluations: walking speed, spatiotemporal parameters and dorsiflexor muscle strength.

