#### Randomisation

Eligible patients who agree to participate will be asked to give their written informed consent, and will then be randomised into the EG or CG. We will randomise the patients at the first clinical examination. The randomisation process will be ensured using a secure internet connection with access by individual user ID and password and encrypted data transmission to the randomisation platform of the Clinical Research Unit of the Limoges University Hospital. Only the study methodologist will complete and keep the randomisation list on a secure server. In the event of a computer problem, a paper randomisation list will be available. This randomisation list will not include a stratification factor. All actions carried out on this platform, along with the identity of the person who made the changes, will be automatically archived by audit trail procedure. As soon as a patient is randomised, an email will automatically be sent to all study organisers, i.e. the clinical research assistant, data manager and principal investigator. No strategy is provided for preventing a potential imbalance between intervention and control group allocation.

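### Technical-aid use is compared by an unadjusted chi-square or Fisher test although aid use at inclusion is recorded: the test is valid, but it gives up precision that stratification would recover at no cost

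*Protocol article*

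**What the plan says.** The fifth secondary objective (Protocol article, Objectives {7}) is "to evaluate the impact of the programme on the use of technical aids and on the number of falls between 6 months and 1 year". The secondary endpoint analyses fix the method: "The comparison of the proportion of patients who used a technical aid will be performed by a Pearson’s chi"-square test, replaced by "Fisher’s exact test if at least one theoretical number is <5". They name no covariate and no time point for aid use, and the section on additional analyses {20b} plans none.

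Three other sections bear on this:

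- Eligibility criteria {10} require that "they are able to walk alone at least 10 m with or without technical assistance", so aid users and non-users both enter.
- The inclusion visit records "walking autonomy (Functional Ambulation Classification; FAC) with collection of the technical aids used and the number of falls", so each patient's baseline aid status will be known.
- The Randomisation section says the list carries no stratification factor, and adds: "No strategy is provided for preventing a potential imbalance between intervention and control group allocation".

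The Outcomes section {12} treats aid use as something to describe, apart from the listed secondary outcomes. The sample size {14} concerns walking speed only.

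**The concern.** The objective asks about the programme's effect on aid use, and a between-arm test will be run on it. Whether a patient walks with an aid at inclusion is likely to be a strong predictor of whether that patient uses one later. A two-by-two test leaves that predictable variation in the error term.

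Two things are at stake:

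- **Precision.** The arm difference is estimated with a larger standard error than the collected data allow.
- **Chance imbalance.** With about 30 patients per arm and no stratified allocation, the arms may differ noticeably in baseline aid use. The crude comparison then carries that difference into the result of the one trial that will be analysed.

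**Working it through.** **The plan's own figure.** Inputs from Sample size {14}: difference 0.09 m/s, SDs 0.09 and 0.11, two-sided 5%, power 90%.

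n per arm = (1.960 + 1.282)² × (0.09² + 0.11²) / 0.09² = 10.51 × 0.0202 / 0.0081 = 26.2, so 27 per arm and 54 in total. Adding 10% gives 59.4, and dividing by 0.9 gives 60. Both lead to the stated 60. The figure reproduces, but it says nothing about aid use.

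**Inputs for aid use.** The documents give no baseline prevalence, later rates or association between them. Everything below is assumed, with 27 or 30 patients per arm. The analysis is taken to concern use at a follow-up visit, since no time point is named.

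**Scenario (a) by hand.** 50% use an aid at baseline. Later use among them is 90% (control) and 50% (experimental); among the others it is 10% in both arms. There are 27 per arm.

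- Marginal later use: control 0.5 × 0.9 + 0.5 × 0.1 = 0.50; experimental 0.5 × 0.5 + 0.5 × 0.1 = 0.30. The true difference is -0.20.
- SD of the crude difference: √[(0.5 × 0.5 + 0.3 × 0.7)/27] = √(0.46/27) = 0.130.
- SD of the stratified difference: the within-stratum part is [(0.5 × 0.09 + 0.5 × 0.09) + (0.5 × 0.25 + 0.5 × 0.09)]/27 = 0.26/27 = 0.00963. The part from the varying share of users is 0.4² × 0.5 × 0.5/54 = 0.00074. Together √0.01037 = 0.102.
- Planned power: the null SE is √(0.4 × 0.6 × 2/27) = 0.133, so the critical difference is 1.96 × 0.133 = 0.261. Power ≈ Φ[(0.200 - 0.261)/0.130] = Φ(-0.47) ≈ 32%.
- Stratified power: the mean pooled within-stratum variance is 0.5 × 0.21 + 0.5 × 0.09 = 0.15. The null SE is √(0.15 × 2/27) = 0.105, and the critical difference is 0.207. Power ≈ Φ[(0.200 - 0.207)/0.102] = Φ(-0.065) ≈ 47%.

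Simulation gives 31% and 48%, in agreement.

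**Simulated power, planned rule against Cochran-Mantel-Haenszel stratified by baseline use.** Later rates are control vs experimental where they differ. The first four rows used 6,000 trials each; repeat runs agreed to within about 2 points. The last five used 20,000 trials each and a treatment log odds ratio of -1.5.

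| Per arm | Baseline use | Later use, baseline users | Later use, others | Planned | Stratified |
|---|---|---|---|---|---|
| 27 (a) | 50% | 90 vs 50% | 10% both | 31% | 48% |
| 27 (b) | 60% | 70 vs 30% | 5% both | 49% | 58% |
| 27 (c) | 70% | 80 vs 40% | 5% both | 54% | 70% |
| 27 (d) | 60% | 90 vs 50% | 10 vs 5% | 48% | 71% |
| 30, weak | 50% | 60% control | 40% control | 72.5% | 73.6% |
| 30, moderate | 50% | 70% control | 20% control | 55.0% | 63.9% |
| 30, strong | 50% | 80% control | 10% control | 37.3% | 54.8% |
| 30, very strong | 50% | 90% control | 5% control | 18.6% | 37.1% |
| 30, strong | 70% | 80% control | 10% control | 51.5% | 65.0% |

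The gain runs from 73.6 - 72.5 = 1.1 points (weak prediction) to 71 - 48 = 23 points in (d).

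**Type I error.** With no effect, the planned test rejects in 4.1-5.3% of the 20,000-trial runs and the stratified test in 3.5-5.2%. The mean arm difference is about 0.

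**Chance imbalance.** With 27 per arm and 50-60% baseline use, the arms differ by 15 points or more in 21-22% of trials. With 30 per arm, they differ by 20 points or more in 12-15% (baseline use 70% or 50%).

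With no effect, a given baseline difference shifts the expected crude difference by that amount times the gap in later use. For 15 points and later use of 90% against 10%, the shift is 0.15 × 0.80 = 12 points. For 60% against 40% it is 0.15 × 0.20 = 3 points.

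Among trials imbalanced by at least 15 points, the planned test rejects a true null in about 16% (later use 90%/10%, baseline use 50%), 13% (80%/10%, baseline use 60%) or 10% (70%/20%, baseline use 50%). The stratified test stays at 4-5% in the same trials.

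**The case against.** A reader might infer that the planned test confounds pre-existing aid use with the programme's effect. The documents do not support that. Allocation is randomised 1:1, so baseline users are balanced in expectation. The overall error rate already includes the imbalanced trials, and the simulated mean difference under no effect is about zero. The statement that no strategy prevents imbalance makes chance differences more likely than under stratified allocation, but it does not invalidate the test.

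A reader might also infer that patients who never needed an aid dilute the effect and that stratifying would undo this. It would not. The Mantel-Haenszel risk difference averages over the same patients: in scenarios (a), (b) and (c) the crude and stratified differences have the same mean (-0.198, -0.242 and -0.283). Only the spread shrinks, in (a) from about 0.13 to 0.10.

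It is fair to add that scenarios (a) to (d) are favourable, each with a 40-point drop among baseline users. Halving that drop in (a) to (c) leaves power at 10% vs 18%, 15% vs 19% and 16% vs 25%, so the objective is underpowered with either test. Aid use is also a secondary matter, no power is claimed for it, and the Outcomes section calls it descriptive. That limits the importance of the point.

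A final objection is that a condensed article may leave covariates to the full protocol or analysis plan. That would hold if the article were silent. It is not: it names a specific test that has no place for a baseline variable.

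**Conclusion.** The point holds as a minor matter of efficiency. The planned comparison of aid use is valid and unbiased on average, but it sets aside a baseline value that the trial already records, and it leaves this one trial's result open to chance imbalance in that value. Under assumed rates, stratifying gains from about 0 to roughly 20 points of power or slightly more, with type I error kept at about 4-5%. Where in that range the trial falls depends on how strongly aid use at inclusion predicts later use, which the documents do not say. The point also assumes that the test concerns follow-up use as a yes/no variable. It does not touch the primary outcome or the sample size.

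**What to change.** In the secondary endpoint analyses, replace the Pearson/Fisher comparison of technical-aid use with a Cochran-Mantel-Haenszel test stratified by aid use at inclusion (yes/no), using the exact stratified version if cells are sparse. Report the Mantel-Haenszel risk difference with its 95% CI, and keep the crude proportions by arm as description.

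The cost is one sentence of text and a standard SAS option, with no new data, visits or patients. The small drawback is that a stratum in which every patient, or none, uses an aid at follow-up adds nothing to the test. The change should be fixed before the allocation is revealed to the analysts.

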### Methods for additional analyses (e.g. subgroup analyses) {20b}

N/A; no methods for additional analyses.

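### The objective 6 correlations between strength, walking speed and SIPSO use post-treatment values with no term for arm, so the coefficient mixes the difference between arms with the association within arms

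*Protocol article*

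**What the plan says.** In the Protocol article, Objectives {7}, the sixth secondary objective is "to evaluate the relationship between dorsiflexor muscle strength, walking speed and social participation".

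The section on secondary endpoint analyses names the pairs and the visits:

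- "dorsi-flexor muscle strength (2 parameters) and walking speed at 6 weeks, 6 months, and 1 year"
- "dorsi-flexor muscle strength (2 parameters) and SIPSO score at 6 months and 1 year"
- "walking speed and SIPSO score at 6 months and 1 year"

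The method is that these "will be performed using the Pearson or Spearman correlation coefficient test", the choice between the two resting on whether their conditions are met. Counting SIPSO as one score, this makes 2 × 3 + 2 × 2 + 2 = 12 coefficients, all from visits after randomised treatment.

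The outcomes section adds only that "correlations between walking speed/dorsiflexor muscle strength and walking speed/social participation will be studied". None of these places mentions arm, a partial correlation or coefficients by arm. The section on additional analyses {20b} reads "N/A; no methods for additional analyses".

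**The concern.** The hypothesis that closes the background section, and the Discussion, expect the programme to improve motor control and strength, then walking, then participation. Randomised arm is therefore a potential common cause of both variables in every pair. If both respond, patients in the experimental arm tend to be higher on both, and a coefficient over all patients picks this up even when, within each arm, stronger patients walk no faster than weaker ones.

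The strength-speed link is part of the trial's mechanistic rationale. If the programme works on both variables, a significant simple correlation could be cited in support of that link although it reflects only the difference between arms. If the programme works on one variable only, pooling adds unrelated variance to that variable and weakens a real association.

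**Working it through.** **Inputs.** From Sample size {14}: walking speed 0.58 (SD 0.09) and 0.67 (SD 0.11) m/s, difference 0.09 m/s, two-sided 5% level, 90% power, 27 per group evaluable, 30 per group included. Allocation is 1:1. The documents give no treatment effect for peak torque, active amplitude or SIPSO, and none for walking speed at 6 months or 1 year. These are assumed over a range.

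**The plan's own figure.** Common SD = √((0.09² + 0.11²)/2) = 0.1005. By the normal approximation, n per group = 2 × (1.960 + 1.282)² × 0.1005²/0.09² = 26.2, rounded up to 27, so 54 in total. Adding 10% gives 59.4, rounded up to 60. The stated size reproduces. The standardised effect on walking speed at 6 weeks is d₁ = 0.09/0.1005 = 0.896.

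**Pooled correlation.** With equal arms, correlation r within each arm, and standardised effects d₁ and d₂ on the two variables:

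r_pooled = (r + d₁d₂/4) / √((1 + d₁²/4)(1 + d₂²/4))

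**No correlation within arms (r = 0), d₁ = 0.896.** For d₂ = 0.5: (0.896 × 0.5/4)/√(1.2007 × 1.0625) = 0.112/1.1295 = 0.10. For d₂ = 0.896: 0.2007/1.2007 = 0.17. The rejection rates come from 40,000 simulated trials per row, normal data, N = 54, two-sided 5% Pearson test:

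| Assumed effect on second variable, d₂ | Pooled correlation | Pooled test, p < 0.05 | Arm-adjusted partial correlation, p < 0.05 |
|---|---|---|---|
| 0 | 0.00 | 5% | 5% |
| 0.2 | 0.04 | 6% | 5% |
| 0.5 | 0.10 | 11% | 5% |
| 0.896 | 0.17 | 23% | 5% |
| 1.2 | 0.21 | 34% | 5% |

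With all 60 patients, the last two pooled rates are 26% and 38%. If both effects are 0.5, the pooled correlation is 0.06 and the rate about 7%. Over all scenarios the partial correlation was significant in 4.9% to 5.2% of trials.

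**A real correlation within arms (r = 0.5), d₁ = 0.896.**

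- d₂ = 0.896: (0.5 + 0.2007)/1.2007 = 0.58
- d₂ = 0.5: (0.5 + 0.112)/1.1295 = 0.54
- d₂ = 0: 0.5/√1.2007 = 0.46

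**The case against.** **Pooling is inferred.** The article names the type of coefficient and does not say that the arms are combined. It condenses a full protocol, and an analysis plan may exist; either could call for partial or by-arm correlations. The entry under additional analyses does not rule that out. This stands, and it is why the point is put as the natural reading of the text. The article does go beyond silence, though: it names a test, and that test has no arm term.

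**The marginal association is a legitimate target.** Objective 6 speaks of a relationship and does not say that it is meant within arms. If both effects are 0.896, the population correlation over both arms really is 0.17, and the 23% is power to detect it. This also stands in part: 23% is a false-positive rate only for the within-arm question. But a correlation over a 1:1 mixture of trained and untrained patients depends on the allocation ratio and the size of the treatment effect. It is a poor answer to whether stronger patients walk faster.

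**The zero-correlation case goes against the trial's premise.** The background section reports dorsiflexor strength as strongly correlated with walking. With a correlation of 0.5 within arms, pooling would not change the qualitative conclusion. This stands and limits the importance of the point.

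**Two stronger readings are tempting, and the documents support neither.** A reader might infer that the plan's own assumptions imply a rejection rate of nearly one in four. They do not, because the 0.896 is documented for walking speed at 6 weeks only. Applying it to strength or SIPSO, or to later visits, is an assumption; for the strength-SIPSO pair neither effect is documented. A reader might also say that the planned test shows a correlation where none exists within patients. These are correlations between patients at single visits, and neither the simple nor the adjusted coefficient measures association within a patient. The relevant null is no correlation within arms.

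**Conclusion.** The point holds as a minor one. As written, the objective 6 analysis is a simple correlation of post-treatment values with no arm term. Read as one coefficient over both arms, it mixes the between-arm difference with the within-arm association.

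The size depends on the undocumented effect on the second variable. With no correlation within arms and 54 patients, the distortion runs from none, if only walking speed responds, to 0.17 and 23% significant results if the second effect equals the design effect; a still larger second effect would give more. With a correlation of 0.5 within arms, the pooled value lies between 0.46 and 0.58 for second effects from 0 to 0.896. The figures assume normal data, equal arms and the same correlation in both arms.

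It should not be read as a threat to the trial's main conclusion: the primary comparison at 6 weeks and the sample size do not use these correlations.

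**What to change.** In the section on secondary endpoint analyses, make the arm-adjusted partial correlation (Pearson or rank), or a regression with arm as covariate, the main analysis for objective 6. Report the pooled and by-arm coefficients alongside, labelled as such. If the full protocol or analysis plan already provides for this, one sentence in the article would settle the point.

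The cost is one line of text, one line of code and one degree of freedom (51 instead of 52 with 54 patients). No extra patients, visits or data are needed.
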